#### 2.8.3. Secondary outcomes

A scale to assess changes in the level of ADL (autonomy) is Modified Barthel Index (MBI).

Modified Barthel Index is a five-level rating scale and evaluates the functional independence and autonomy of the subjects in 10 activities, including (1) bathing, (2) personal grooming, (3) feeding, (4) dressing and undressing, (5) bowel, (6) bladder continence, (7) getting on/off the toilet, (8) stair climbing, (9) moving from wheelchair to bed and return, and (10) walking, with high reliability and stability in people of different sexes and ages (44). The highest score of the MBI is 100, with higher scores indicating increased ADL.

### 2.9. Adverse events

A safety questionnaire will be administered to all participants prior to the administration of the first PA or EMT to reduce the risk of possible symptoms, including dry eyes, headache, and irritability, and will be recorded at the end of each session. Descriptive statistics will be provided for all adverse events.

The following measures will be taken to prevent these events: (a) prior to the intervention, the investigator will communicate adequately to ensure that the patient is in a good state after rest; (b) during the intervention, the investigator will closely monitor the patient's condition and keep records; (c) if the patient feels any discomfort, the intervention will be suspended immediately, the intervention protocol will be adjusted (by increasing the interval of rest), or the intervention will be stopped. If a serious adverse event occurs, we will seek professional evaluation, cover the cost of treatment for the adverse event caused by the trial, and provide some financial compensation.

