**Methods:**

We will conduct a single-blind, prospective, randomized controlled trial to assess the efficacy of the combined intervention (PA & EMT) on USN in an inpatient rehabilitation setting. The study aims to recruit 88 patients with USN after an ischemic or hemorrhagic stroke. Participants will be randomly assigned to the following four groups: (1) PA group (*n* = 22), (2) EMT group (*n* = 22), (3) PA and EMT group (*n* = 22), and (4) control group (*n* = 22). All groups will receive 10 sessions of interventions over 2 weeks, 5 times per week. Blinded assessors will conduct a baseline assessment, a post-intervention assessment, and a follow-up assessment (2 weeks post-intervention). The primary outcome measure will use the Behavioral Inattention Test-Conventional Subset (BIT-C) and Catherine Bergego Scale (CBS) to assess the levels of USN. Secondary outcome measures will assess the patient's ability to perform activities of daily living using the Modified Barthel Index (MBI). Patients who completed all treatment and assessment sessions will be included in the final analysis.

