**Discussion:**

This study will explore the effects of 10 sessions of combined interventions (PA & EMT) on USN and functional capacity. This study has the potential to identify a new, evidence-based treatment option and provide new ideas for the treatment of USN.

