#### 2.6.3. Eye movement training

The eye movement training will be performed based on a high-performance EMT instrument (Figure 2, Hangzhou Jizhi Medical Technology Co., Ltd., Model: JZ-RZ-20US). The insect shoot-down task of the cognitive rehabilitation training and assessment system will be selected as the EMT task (search and gaze). The insect shoot-down task will be set at easy, moderate, and difficult levels (depending on the patient's training performance), left or right field of view (the choice of left or right visual field depends on the patient's side of neglect), during which the insect will randomly present on the left or right side of the screen and move from bottom to top. Under the guidance of the therapist, the patient spontaneously searches for these signs, eliminates them by gazing, and then searches for the next sign until the end of the training. At the same time, this eye-tracking device has an eye-tracking function, which can visually show the patient's eye movement trajectory and facilitate the therapist to better train the patient. The EMT schedule was 15 min/session, 1 session/day, and 5 days/week, with a treatment period of 2 weeks.

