### 2.10. Dropout criteria

The intervention will be discontinued if the subject meets one or more of the following criteria: (a) the subject has poor compliance and fails to perform the treatment as required, e.g., the subject does not cooperate with the investigator or the subject does not come to treatment on time; (b) medical records are incomplete and affect efficacy or safety evaluation; (c) subject voluntarily withdraws; (d) subject experiences an adverse event (including episodes of ocular pain, headache, and irritability); and (e) the subject has a severely progressive disease or some comorbidity, complications, or specific physiological changes.

Patients who drop out will not be included in the efficacy analysis; if they drop out for reasons such as the occurrence of an adverse event, they will be included in the safety analysis.

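### The adverse-event questionnaire is timed by PA and EMT sessions, so like-for-like symptom capture across the four arms, control included, is not assured

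*Protocol article*

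**What the plan says.** Protocol article, section 2.9, sets the collection rule: "A safety questionnaire will be administered to all participants prior to the administration of the first PA or EMT". The same sentence names dry eyes, headache and irritability and adds that they "will be recorded at the end of each session". The section promises descriptive statistics for all adverse events.

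The number of sessions is given in several places:

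- Abstract, Methods: "All groups will receive 10 sessions of interventions over 2 weeks, 5 times per week".
- Abstract, Discussion: "This study will explore the effects of 10 sessions of combined interventions (PA & EMT) on USN and functional capacity".
- Table 1 heads the intervention column with 2 weeks and 10 sessions.
- Section 2.6.2 schedules PA once a day, 5 days a week, for 2 weeks.
- Section 2.6.3 does the same for the other component: "The EMT schedule was 15 min/session, 1 session/day, and 5 days/week", also for 2 weeks.
- Section 2.6.1, on conventional rehabilitation, gives no session unit, length or frequency.

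The control group has 22 patients (abstract; group D in section 2.5). Section 2.10 lists as a discontinuation criterion that the "subject experiences an adverse event (including episodes of ocular pain, headache, and irritability". It keeps dropouts out of the efficacy analysis, though those who leave because of an adverse event stay in the safety analysis.

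**The concern.** A rule meant for everyone is fixed to an event that one arm never has. Headache, irritability and dry eyes can occur in subacute stroke inpatients without any training, so a count in the trained arms means little without a control count collected in the same way. If staff at the site read the rule as applying only where PA or EMT is given, the safety table would set symptoms in three arms against an empty or informally filled column in the fourth.

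The unclear session adds to this. Two therapists could each follow the text in the combined arm and complete the form once or twice on the same day.

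The matter may also reach efficacy. Headache and irritability appear both in the symptom list of section 2.9 and in discontinuation criterion (d) of section 2.10, and a patient who drops out leaves the efficacy analysis. How symptoms come to notice should therefore be the same in every arm.

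**Working it through.** **1. The article's own session count.** 5 sessions per week × 2 weeks = 10, which reproduces the 10 sessions stated for every group.

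**2. The starting point, arm by arm.** The questionnaire precedes the first PA or EMT. That event exists in the PA, EMT and combined arms. Section 2.1 names only three kinds of training for four groups, and section 2.6 gives every patient conventional rehabilitation plus the group's own intervention, so the control arm is taken to receive conventional rehabilitation alone. The starting point is then missing for 22 of 88 patients: 22 / 88 = 25%. Section 2.1 gives a total of 72 instead of 88; with 1:1:1:1 allocation the share is one quarter either way.

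**3. The recording unit, arm by arm.**

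| Arm | What a session is | End-of-session recordings |
|---|---|---|
| PA | daily PA session (2.6.2) | 10 |
| EMT | daily EMT session (2.6.3) | 10 |
| Combined | 10 combined sessions (abstract, Table 1), or daily PA and daily EMT sessions (2.6.2, 2.6.3) | 10 on the stated count; not defined by 2.9 |
| Control | 10 sessions by the abstract; no session described in 2.6.1 | not determined |

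Only the two single arms have an unambiguous count.

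**4. Period covered.** T0 to T2 is 2 weeks of treatment plus 2 weeks of follow-up, 4 weeks in all. End-of-session recording covers the first 2. Section 2.8 places outcome scales at T1 and T2 but does not mention adverse events, and Table 1 has no adverse-event row.

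**5. What a missing control count could do (illustration only).** Suppose controls were not recorded, training had no effect on symptoms, and each recording had an independent chance p of showing a background symptom. The expected number of patients with at least one event among 22 in a trained arm with 10 recordings is 22 × [1 − (1 − p)^10]:

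- p = 1%: 22 × 0.096 = 2.1
- p = 2%: 22 × 0.183 = 4.0
- p = 5%: 22 × 0.401 = 8.8

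The control count would be 0. The values of p are assumptions, since the article gives none. Recordings in one patient are likely to be correlated, which would lower these figures.

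**The case against.** The other side has four good arguments.

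*Controls are named.* Section 2.9 says all participants, the abstract gives 10 sessions to all groups, and section 2.6.1 calls conventional rehabilitation an intervention. End-of-session recording can therefore be read to include controls. This stands against any claim that controls are never asked. It does not supply the missing starting point, or say which part of a day of physical therapy, occupational therapy and acupuncture closes a session.

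*The combined arm has 10 sessions.* A reader might add the two component schedules, 10 + 10 = 20, and infer that combined-arm patients are asked twice as often and will look less safe for that reason. The documents do not support this. The abstract counts 10 combined sessions, Table 1 agrees, and nothing says the form is completed after each component. On the stated count the ratio is 10 / 10 = 1. Only the lack of a definition remains.

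*Silence after treatment is not a gap in capture.* A reader might infer that nothing is collected between the last session and T2. The article is a condensed account, and the full protocol or case report form may cover this period. The missing row in Table 1 proves little: the table also shows no baseline tick for the three outcome scales that section 2.7 says are collected before randomization. What can be said is that no recording point is stated.

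*Discontinuation does not depend on the form.* Section 2.9 also provides that "during the intervention, the investigator will closely monitor the patient's condition and keep records", and criterion (d) turns on experiencing an event. Unequal form-filling therefore need not produce unequal discontinuation. The link to the efficacy analysis is a reason for care and has not been shown as a bias.

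Safety is also reported descriptively only, with no between-arm test stated, which limits the weight of the point.

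**Conclusion.** The point holds as an inconsistency in the stated collection rule. The rule addresses all participants, but its starting point does not exist for one quarter of them, its recording unit is undefined for controls and for the combined arm, and it states no recording point for 2 of the 4 weeks from T0 to T2. Comparable capture of background symptoms across the arms is not assured. The direction and size of any distortion cannot be derived from the article, because they depend on how the site reads the rule and on a background symptom rate that is not given. The conclusion assumes that controls receive conventional rehabilitation only. This is a cheap improvement worth making. It is not evidence that the safety data are already unequal.

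**What to change.** Replace the session-based rule in section 2.9 with one symptom-questionnaire schedule for all four arms: once at baseline, once per treatment day on each of the 10 days (controls included, and only once per day in the combined arm), and at the existing T1 and T2 visits. That is 1 + 10 + 1 + 1 = 13 planned recordings per patient in every arm. Add an adverse-event row to Table 1. Report the number of patients with each event by arm from this schedule, and list symptoms volunteered during sessions separately so that extra contact time does not enter the comparison.

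The cost is the wording, one table row and a few minutes of form-filling per day for the 22 control inpatients. Treatment, visits and staffing do not change. As recruitment is under way, the date of the change should be recorded, and events captured before and after it shown separately.

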### 2.10. Dropout criteria

The intervention will be discontinued if the subject meets one or more of the following criteria: (a) the subject has poor compliance and fails to perform the treatment as required, e.g., the subject does not cooperate with the investigator or the subject does not come to treatment on time; (b) medical records are incomplete and affect efficacy or safety evaluation; (c) subject voluntarily withdraws; (d) subject experiences an adverse event (including episodes of ocular pain, headache, and irritability); and (e) the subject has a severely progressive disease or some comorbidity, complications, or specific physiological changes.

Patients who drop out will not be included in the efficacy analysis; if they drop out for reasons such as the occurrence of an adverse event, they will be included in the safety analysis.

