### 2.5. Randomization and blinding

A random number list is generated by a computer and consists of 88 random numbers. The random numbers were arranged from the smallest to the largest to obtain the serial number R. It is stipulated that group A (PA) with *R* = 1–22, group B (EMT) with *R* = 23–44, group C (PA & EMT) with *R* = 45–66, and group *D* (control) with R = 67–88. The resulting sequence of random assignments was placed in sequentially coded, sealed, impermeable envelopes. The investigator in charge of recruitment opens the envelope according to the order of patient enrollment and assigns the subjects to the appropriate subject group.

This study is a single-blind design, and only the investigator conducting the assessment is blinded to group assignment. The therapist cannot be blinded due to using the supervised intervention. In addition, blinding of subjects is not feasible due to the difference in intervention methods. All outcome assessments for this study will be conducted by a separate professional therapist who is not involved in any other part of the study. Moreover, participants will be unblinded when any clinical situation associated with adverse events or patient withdrawal occurs.

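### The efficacy analysis keeps only completers, so patients stopped under section 2.10, including for adverse events plausibly due to the training, are removed after randomisation

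*Protocol article*

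**What the plan says.** Section 2.10 opens with a rule: "The intervention will be discontinued if the subject meets one or more of the following criteria". The five criteria are (a) poor compliance, (b) incomplete records, (c) voluntary withdrawal, (d) an adverse event and (e) serious progression, comorbidity or complications. Criterion (d) reads "subject experiences an adverse event (including episodes of ocular pain, headache, and irritability"), with no grade, seriousness or causality attached.

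The section then fixes the consequence: "Patients who drop out will not be included in the efficacy analysis". Patients who leave because of an adverse event are kept for safety. The abstract's Methods paragraph says the same from the other side: "Patients who completed all treatment and assessment sessions will be included in the final analysis".

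Three other places bear on this:
- **Section 2.9** names dry eyes, headache and irritability as possible symptoms around PA and EMT. Its preventive measures ("The following measures will be taken to prevent these events") include, at point (c), this one: "if the patient feels any discomfort, the intervention will be suspended immediately, the intervention protocol will be adjusted (by increasing the interval of rest"). Stopping treatment is the last of the options given there.
- **Section 2.11** undertakes to collect as much data as possible from patients who discontinue, for further analysis. It does not say that these data enter the efficacy analysis.
- **Section 2.5** states that "only the investigator conducting the assessment is blinded to group assignment".

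**The concern.** Randomisation protects a comparison only while patients are analysed as allocated. Here, events after randomisation decide who is analysed, and at least one of them, an adverse event during training, can be caused by the treatment under test. If patients who stop would have done worse (or better) than those who finish, and if stopping is not equally common in each arm, the completers' difference no longer estimates the effect of assignment.

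The other criteria work the same way. Poor compliance and voluntary withdrawal may also depend on how demanding the assigned training is. Criterion (d) is the clearest example, because two of its three listed symptoms are ones that section 2.9 itself expects around PA and EMT.

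**Working it through.** **1. Does any text return stopped patients to the efficacy analysis?** No. Section 2.10 excludes them and the abstract excludes anyone who missed a treatment or assessment session. Section 2.11 collects their data without assigning them to an efficacy analysis, and section 2.12 names no as-randomised or sensitivity analysis.

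**2. Is the exclusion plausibly related to treatment?** Training time over 10 sessions, from sections 2.6.2 and 2.6.3:
- EMT: 10 × 15 = 150 min.
- PA: 10 × (15 to 20) = 150 to 200 min.
- Combined: 150 + (150 to 200) = 300 to 350 min. This assumes that both are given in full, which the Introduction's description of sequential use suggests but does not state.
- Control: 0 min. This is the likely reading but not an explicit one. The abstract gives every group 10 sessions of interventions, and section 2.1 says all patients get one of three types of training.

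Exposure to the anticipated symptoms therefore differs by arm. Therapists and patients know the arm. The article does not say who classifies a symptom as an adverse event. That unblinded staff do so is an inference from section 2.5.

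**3. The plan's own figures.** Section 2.4 gives pilot BIT-C changes of 39.33 (SD 18.717) for combined, 26.33 (SD 7.638) for EMT and 20 (SD 2.828) for PA. The differences are 39.33 − 26.33 = 13.00 and 39.33 − 20 = 19.33. A two-sample t-test with 2n − 2 degrees of freedom, SE = √((s₁² + s₂²)/n) and two-sided α 0.05 has power 0.800 at n = 20 and 0.820 at n = 9. The stated 20 and 9 therefore reproduce. Adding 10% gives 20 × 1.10 = 22 per group and 88 in total.

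**4. How large could the bias be?** The article gives neither an event rate nor outcomes for stopped patients, so this is illustration only. Suppose k of 22 patients in an arm are excluded and would have gained d points less than that arm's completers. The completers' mean then overstates the arm's mean by k·d/22. For combined minus EMT:

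bias = (k_C·d_C − k_E·d_E)/22

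With d from 0 to 13 (assumed; the top of the range is the pilot difference):

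| Exclusions | Bias (BIT-C points) |
|---|---|
| 3 in combined, 0 in EMT | 0 to 3 × 13/22 = +1.8 |
| 0 in combined, 3 in EMT | 0 to −1.8 |
| Equal numbers, equal deficits | 0 |

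The largest entry is 1.77/13 = 14% of the pilot difference.

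**5. Effect on type I error, under assumptions.** The simulation had no true difference, 22 per arm, the pilot SDs, a Welch test and exclusion in the SD 18.717 arm only. The rejection rate was 4.9% with no exclusion. It was 5.5% with 10% excluded and a 10-point deficit, 6.8% with 20% and 10 points, and 11.8% with 20% and 18.7 points.

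**6. Is lost power the harm?** No. Take three losses in combined only, with a 13-point deficit. Welch power for completers is 0.774 (19 versus 22, difference 13). With those patients kept, the difference is 13 − 1.77 = 11.23 and power at 22 versus 22 is 0.710. In this scenario the right analysis has less power. The case rests on bias.

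**The case against.** **The stopping rule.** A reader might infer from 2.10(d) that any headache, however slight, ends treatment. That is its literal wording, but 2.9(c) lets discomfort be met with a pause or more rest as well as with stopping. Read together, the two sections do not establish that every mild symptom ends treatment. What stands is that the line between discomfort and an adverse event is not drawn. This is a minor matter of wording.

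**Power.** A reader might also infer that the exclusions threaten the planned power and that keeping the patients would restore it. Step 6 shows the reverse in one plausible scenario, so lost power is not a measure of harm here.

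**Size.** The bias is hypothetical, may run in either direction and is modest in the scenarios shown. Controls can also meet 2.10(d). All of this stands, and it limits the claim to plausible bias of unknown size. Section 3 reports that the training was well tolerated, but only from the few patients who had completed it, so it says nothing about those who stop.

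**An unseen analysis plan.** The article is not silent on the efficacy population. It fixes it in two places, so the point does not depend on anything left to a separate document.

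**Conclusion.** The concern holds as a weakness in the analysis population. As written, every patient stopped under any criterion in 2.10 leaves the efficacy analysis after randomisation. For adverse events the link to treatment is plausible: section 2.9 anticipates the symptoms, exposure differs by arm, and only the assessor is blinded.

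The size and direction of the bias cannot be determined from the document. The ±1.8 points and the type I error rates above rest on assumed numbers of exclusions and assumed deficits. The conclusion does not need them: it follows from the two exclusion statements and the differing exposure. The sponsor should change this, but the document does not show that the trial's result would be materially wrong.

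**What to change.** Amend section 2.10 and the abstract's Methods paragraph as follows:
- Stopping the intervention for any reason in 2.10 does not end participation. T1 and T2 assessments still take place unless the patient withdraws consent to follow-up.
- The primary efficacy analysis includes all randomised patients with outcome data, in their assigned group.
- Sessions received and reasons for stopping are reported by arm.
- The completers analysis is kept as a sensitivity analysis.

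The rule for stopping treatment is not loosened, so patient safety is unaffected. As a minor clarification, align the wording of 2.9(c) and 2.10(d) so that staff know when discomfort becomes an adverse event that stops treatment. Any clinical threshold is for the investigators to set.

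The cost is a protocol amendment during recruitment, which began on 2 November 2021 and was ongoing at publication. No extra patients or visits are needed, since T1 and T2 are already scheduled and section 2.11 already intends to collect data after discontinuation. The effect estimate will be somewhat diluted by patients with fewer sessions, and power may fall. Patients who have already discontinued may lack T1 or T2 data. Their number should be reported by arm.

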### 2.11. Data collection and management

The trial process will be recorded *via* the audio or written form to ensure the authenticity of the intervention. A case report form (CRF) will be used to collect data. Two data managers will enter the data from the CRF into a computer database and cross-check the electronic data for uniformity. All data will be confidential to those outside the study, except for the ethics committee. Experimental data will be used to write clinical research studies. During the course of the study, if subjects discontinue or deviate from the intervention protocol, we will collect as much data as possible for further analysis.

We will use the following methods to facilitate participants' completion of the trial and follow-up: (a) enhance communication between investigators and patients and obtain patients' cooperation whenever possible and (b) provide relevant test results to study patients free of charge.

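### The efficacy analysis keeps only completers and drops randomised patients for post-randomisation reasons, so the arm comparison is open to selection bias of unknown size and direction

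*Protocol article*

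**What the plan says.** Two places in the protocol article define who is analysed for efficacy.

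- Abstract, Methods: "Patients who completed all treatment and assessment sessions will be included in the final analysis".
- Section 2.10: "Patients who drop out will not be included in the efficacy analysis". Those who leave for reasons such as an adverse event are kept for safety only.

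Section 2.10 lists five grounds for discontinuing the intervention and treats a patient who meets any of them as a dropout:

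- (a) "the subject has poor compliance and fails to perform the treatment as required", with lateness and non-cooperation as examples;
- (b) "medical records are incomplete and affect efficacy or safety evaluation";
- (c) voluntary withdrawal;
- (d) an adverse event, with ocular pain, headache and irritability named;
- (e) "the subject has a severely progressive disease or some comorbidity, complications, or specific physiological changes".

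Section 2.11 adds that "if subjects discontinue or deviate from the intervention protocol, we will collect as much data as possible for further analysis". It names no visits, scales or analysis for those data. Section 2.12 plans one-way ANOVA or Kruskal-Wallis across the four groups at T1 and T2. It does not mention an as-randomised population.

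**The concern.** Randomisation makes the four groups comparable at entry. An analysis set chosen by what happens afterwards keeps that comparability only if the selection acts alike in every arm. All five grounds in Section 2.10 arise after allocation, and three features of the plan make unequal selection plausible.

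- **Judgement without blinding.** Poor compliance, and records incomplete enough to affect evaluation, are matters of opinion. Section 2.5 blinds only the outcome assessor, who takes no other part in the study. Whoever applies the criteria, and the patients who withdraw, can therefore know the arm.
- **Different burden.** The combined arm receives both PA and EMT. Section 2.9 ties the expected symptoms (dry eyes, headache, irritability) to these trainings.
- **A stated worry about tolerance.** The Discussion warns that a badly chosen combination can worsen neglect. It also counts the need for active participation in both trainings as a possible limitation. A patient who does badly and stops is the one the rule removes.

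Both primary outcomes (BIT-C and CBS) and the secondary outcome (MBI) are affected. Read literally, the abstract is also stricter than Section 2.10: missing one of the ten sessions, or only the follow-up visit, would remove a patient from every comparison.

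**Working it through.** **Inputs** (Section 2.4 unless noted). BIT-C change: combined 39.33 (SD 18.717), EMT 26.33 (SD 7.638), PA 20 (SD 2.828). α = 0.05, two-sided (Section 2.12). Power 80%. Dropout 10%. 22 patients per arm.

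**1. The plan's own figures reproduce.**
- Combined vs EMT: difference 39.33 − 26.33 = 13.00; SD = √((18.717² + 7.638²)/2) = 14.29. A two-sample t calculation with pooled SD needs 20 per arm, as stated.
- Combined vs PA: difference 39.33 − 20 = 19.33; SD = √((18.717² + 2.828²)/2) = 13.39. It needs 9 per arm, as stated.
- Allowance: 20 × 1.10 = 22 per arm, 88 in total.

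**2. What the 10% allowance does.** With 22 analysed per arm, power for combined vs EMT is 83.8%; with 20 it is 80.0%. Both figures assume the same effect in patients who stay and patients who leave. The allowance replaces lost numbers and does not address who is lost. Ten percent of 22 is 2.2, about two patients per arm.

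**3. Possible bias, illustration A.** Take the pilot means as completer means. If a fraction f of an arm is excluded and would have gained g, the completer mean exceeds the all-randomised mean by f × (completer mean − g). The values of g are assumptions.

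| Pattern, f = 10% | Combined | EMT | Net bias | Share of 13 |
|---|---|---|---|---|
| Same shortfall from own arm's mean, both arms | equal | equal | 0 | 0% |
| Both arms, g = 0 | 0.10 × 39.33 = 3.93 | 0.10 × 26.33 = 2.63 | 1.30 | 10% |
| Both arms, g = 20 | 0.10 × 19.33 = 1.93 | 0.10 × 6.33 = 0.63 | 1.30 | 10% |
| Combined arm only, g = 20 | 1.93 | 0 | 1.93 | 15% |
| Combined arm only, g = 0 | 3.93 | 0 | 3.93 | 30% |

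When g is the same in both arms it cancels, and the net is 0.10 × 13 = 1.30 whatever its value.

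**4. Possible bias, illustration B.** Suppose dropouts lie k SD below their arm's overall mean, with SD 14.29 and k = 0.5 to 1 (assumed). Then bias = [dC/(1 − dC) − dE/(1 − dE)] × k × 14.29, where dC and dE are the dropout fractions in the combined and EMT arms.
- 10% vs 10%: 0.
- 15% vs 5%: (0.1765 − 0.0526) × 14.29 × k = 0.9 to 1.8 points.
- 20% vs 10%: 1.0 to 2.0 points.
- 30% vs 10%: 2.3 to 4.5 points (up to 35% of 13).
- 5% vs 15%: the sign reverses, −0.9 to −1.8 points, against the combined arm.

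The documents give no dropout rates by arm, so none of these patterns can be preferred.

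**The case against.** The strongest reply is that the text shows no bias. The criteria in Section 2.10 apply to every arm. All arms have conventional rehabilitation, so non-compliance, withdrawal and complications can occur anywhere, and either single training could cause the listed symptoms. Selection could also run the other way, for instance if unblinded control patients who recover slowly withdraw. This stands. A reader might infer that poor responders leave the combined arm only and that the result is tilted towards the hypothesis; the documents do not support that.

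The last two rows of the first table are therefore one-sided cases. Zero gain is also severe for patients 1 to 12 weeks after stroke who are receiving rehabilitation.

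It may be said that the data from patients who stop are not thrown away, since Section 2.11 keeps them for further analysis, and that an unseen analysis plan may use them. That is fair for a supplementary analysis. An as-randomised primary analysis, however, would contradict the abstract and Section 2.10 as written, so this is a stated rule and not a detail left for later.

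The Discussion reports that the few patients who completed the intervention found it acceptable. That reassurance itself comes from completers. It also calls the study preliminary and exploratory, yet says positive results could support recommending the techniques.

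Finally, a reader might infer that treated dropouts vanish from the safety analysis. Section 2.9 promises descriptive statistics for all adverse events, and the safety wording in Section 2.10 is not exclusive. The safety denominator is unclear, no more.

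**Conclusion.** The point holds in this form: the plan states a completer-only efficacy set, defined by post-randomisation events, and the document offers no as-randomised analysis. The four-arm comparison is open to selection bias. That it is biased, or biased in favour of the combined arm, is not established.

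Across the assumed patterns in which the combined arm loses as many patients as EMT or more, the bias in combined versus EMT runs from 0 to about 4.5 BIT-C points, against a planned difference of 13. It is 1.3 points with equal 10% exclusion and a common gain among those excluded, and its sign can reverse. These figures rest on pilot means and on assumed dropout patterns and outcomes. Confidence is high about the rule itself and low about the size of its effect. It should be corrected before analysis because it governs every efficacy result and the remedy is cheap.

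**What to change.** In Sections 2.10 and 2.12 and in the abstract:

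- Define the primary efficacy set as all randomised patients, in the group to which they were allocated.
- Separate stopping the intervention from leaving the study. A patient who stops training still has BIT-C, CBS and MBI at T1 and T2 unless consent to follow-up is withdrawn. Section 2.11 already intends such collection and needs only to name these visits and scales.
- Handle values still missing with a likelihood-based repeated-measures model or multiple imputation. The details can sit in the analysis plan.
- Report the completer analysis as a sensitivity analysis, with exclusions by arm and reason.

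As a secondary clarification, define the safety set as all patients who received at least one session, whatever their reason for leaving. Sections 2.9(c) and 2.10(d) must also be reconciled: the first allows suspension, adjustment or stopping after discomfort, while the second lists an adverse event as a ground for discontinuation.

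The cost is some rewording and a modest effort to assess patients who stop. Recruitment began on 2 November 2021 and was ongoing at publication, so patients who have already dropped out may lack T1 or T2 data. The estimate may turn out less favourable.
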